#### *Data management*

The primary data set is generated and managed by the clinical project management of the study management. The data generated on the basis of the CRFs are entered into the central database at the study management using the “double-entry” principle. To ensure optimal data protection, the data on settlement or primary endpoints are stored and evaluated without any reference to the name of the child or the personal data of the parents. Pathogen isolates are stored without patient identifying data but date of collection to allow a temporal and

cluster-related assignment (retrospective detection of transmission by central biobanking and pathogen genotyping). The provisions of the Data Protection Act are strictly adhered to, ensuring the data is safeguarded from third-party access.

#### *Sample size calculation and statistical analysis*

GNN and PRIMAL centers treat on average 150 preterm and critically ill neonates per year with compulsory colonization screening. The center-specific rates of Gram-negative HA infection ranges between 1.5 and 6%. Based on single center data as described above and other cohort studies (20-22) we expect 10% of these infants to be colonized with 2MRGN during hospital stay, i.e. 180 infants per 12 months observational period.

Based on previous data, we assume an intracluster correlation of maximally 0.01. Given that the observed correlation is very low, the time lag between the two trial periods is long and different patients are included in the two trial periods at each site. No carry-over effects are assumed, as we are not expecting that effects of one treatment period would influence the second period (after cross-over) since medical care-givers are aware of the study period they are in. Data from two periods at one site are regarded as two independent sites. We further assume a frequency of Gram-negative HA infections in the controls of 3% and a non-inferiority limit of 5%. Striving for a power of 0.8 ( $1-\beta$ ) with a one-sided significance level  $\alpha$  of 0.05, at least  $n=18$  patients per site and phase are required for analysis with 12 sites, thus  $n=432$  in total. To allow for a maximal drop-out of 10% drop-out, at least 480 patients need to be included.

The primary data analysis will be performed according to the intention-to-treat principle (non-linear mixed effect regression models, logit link). Generalized estimating equations are performed to determine the infection rates between the two regimens. Secondary endpoints are analysed as the primary endpoint per individual or per cluster.

### *Data dissemination*

After completion of the study, the results will be presented at national and international congresses and published in peer-reviewed journals. The results are also presented in the media of the parents' associations (Federal Association "The Pregnant Child" and EFCNI). The public is informed about the study in the form of press releases and background articles on preterm birth and infection risks.

### *Funding*

The study is partially funded by the German Ministry of Education and Research (German Center for Infection Research), the German Society for Pediatric Infectious Diseases and the Damp Stiftung.

### **Perspectives**

The BALTIC study was drafted to create evidence on the effectiveness of extended barrier precaution measures in critically ill newborns being colonized with MDRO. Current guidelines recommend regular screening and the consequent use of gloves and gowns in case of 2MRGN colonization, however, the evidence on clinically relevant outcomes is scarce. Potential disadvantages of extended barrier precautions are time- and cost intensity and may interfere with individualized neurodevelopmental care. The multicenter design of BALTIC creates new insights into center-specific endemic flora of NICUs and population-representative data on MDRO colonization dynamics. Standardized trainings on the proper use of infection control measures will lead to an improved awareness on preventive strategies and the establishment of network platforms including antibiotic stewardship programs. This study also has

limitations. Training and audits will be performed as controlled co-intervention, however, significant variation in compliance due to Hawthorne or observer bias and irregular attendance of healthcare professionals for training lessons cannot be prevented. Considering that there are few studies that have rigorously investigated the current recommendations for infection control in neonatology, BALTIC will contribute to more refined and successful interventions in the future.

## DECLARATIONS

**Statement of Ethics:** The BALTIC study was approved by the institutional review board of the University of Lübeck (primary vote, 19-275) and by the review boards of all participating sites (secondary vote). No identifying data about the infants were collected.

**Consent for publication:** Not applicable

**Availability of data and material:** The full protocol is registered in the German registry of clinical studies (DRKS, Trial registration number: DRKS00019103), we plan to grant access to the full dataset. The datasets used and/or analysed for the benchmarking results are available from the corresponding author on reasonable request.

**Competing interests:** JP received a grant from the German ministry of education and research (#01EO2106). MK has received honoraria for consulting, presentations, expert testimony, and advisory board participation from Abbott, GSK, Pfizer, and Sanofi outside the submitted work. He is member in the board of the AWMF-guidelines “sustainability in intensive care and emergency medicine” and “invasive ventilation and use of extracorporeal oxygenation in patients with respiratory failure” outside the submitted work and has received travel support from the Deutsche Gesellschaft für Hygiene und Mikrobiologie.

The other authors have no conflicts of interest relevant to this article to disclose.

**Funding Sources:** The study was funded by the German Center for Infection Research, the German Society for Pediatric Infectious Diseases and the Damp Stiftung in 2019. The funders had no role in the design, data collection, data analysis, and reporting of this study.

## 1 List of Abbreviations

| Abbreviation | Description                                                                                                               |
|--------------|---------------------------------------------------------------------------------------------------------------------------|
| AE           | Adverse Event                                                                                                             |
| BSI          | Bloodstream Infection                                                                                                     |
| CO           | Control group with hand disinfection plus gloves and gowns                                                                |
| CONSORT      | Consolidated Standards of Reporting Trials                                                                                |
| CRF          | Case Report Form                                                                                                          |
| GEE          | Generalized Estimating Equations                                                                                          |
| IMBS         | Institute of Medical Biometry and Statistics, University of Lübeck, University Hospital Schleswig-Holstein, Campus Lübeck |
| ITT          | Intention-To-Treat                                                                                                        |
| IV           | Intervention group with hand disinfection alone                                                                           |
| MRGN         | Multi-Resistant Gram-Negative                                                                                             |
| n.a.         | not applicable                                                                                                            |
| NICU         | Neonatal Intensive Care Unit                                                                                              |
| R            | R Software                                                                                                                |
| SAP          | Statistical Analysis Plan                                                                                                 |
| SOP          | Standard Operating Procedures                                                                                             |

## 2 Aim of the Statistical Analysis Plan

Central assumptions, methods, and procedures for the statistical analysis are described in the study protocol. The statistical analysis plan (SAP) specifies in detail the statistical and biostatistical approaches and procedures to be used.

The SAP only includes the statistical analyses for which the Institute for Medical Biometry and Statistics, University of Lübeck, University Hospital Schleswig-Holstein, Campus Lübeck (IMBS) is responsible.

The reference documents of the SAP are

- the protocol of 17.07.2019, version 1,
- the publication of the study protocol (Faust et al. Mol Cell Pediatr 2025)

### 3 Responsibilities

For data entry, a central Access database was programmed by the data management of the IMBS according to its standard operating procedures (SOPs).

The primary data set is generated and managed by the clinical project management of the study management. The data generated on the basis of the case report forms (CRFs) are entered into the central database at the study management using the "double-entry" principle. To ensure optimal data protection, the data on settlement or primary endpoints are stored and evaluated without any reference to the name of the child or the personal data of the parents.

For the final analysis, the clinical project management team exports the data and transfers it to the biostatistics team of the IMBS.

Statistical analyses will be carried out by the IMBS, independently of the sponsor's/sponsor's representative interests.

Contact Programmer:

Institut für Medizinische Biometrie und Statistik

Universität zu Lübeck

[name]

Programmer

[name]

[contact]

### 4 Study Design and Amendments

#### 4.1 Study

|                          |                                                                                                              |
|--------------------------|--------------------------------------------------------------------------------------------------------------|
| Full title of the study  | Barrier protection to lower transmission and infection rates with gram-negative bacteria in preterm children |
| Short title of the study | BALTIC                                                                                                       |

|                               |                                                                                                                                                                                                                                                                                                                                                                                                                                                                                                 |
|-------------------------------|-------------------------------------------------------------------------------------------------------------------------------------------------------------------------------------------------------------------------------------------------------------------------------------------------------------------------------------------------------------------------------------------------------------------------------------------------------------------------------------------------|
| Indication                    | Infection with multiresistant gram-negative (MRGN) bacteria with in-vitro resistance to piperacillin and 3rd generation cephalosporins (2MRGN)                                                                                                                                                                                                                                                                                                                                                  |
| Primary objectives            | To show non-inferiority of hand disinfection as compared to hand disinfection + gloves and gowns for the care of 2MRGN colonized infants in neonatal intensive care units (NICUs) with regard to gram negative infections                                                                                                                                                                                                                                                                       |
| Secondary objectives          | To explore non-inferiority with regard to other transmissions and infections on patient- and month-level                                                                                                                                                                                                                                                                                                                                                                                        |
| Study design                  | Cluster-randomized, cross-over, two-arm, multicentric, open                                                                                                                                                                                                                                                                                                                                                                                                                                     |
| Randomization procedure       | Randomization of sequence of interventions for every site, i.e. randomization of clusters stratified by site, by a computerized simple sequence tool                                                                                                                                                                                                                                                                                                                                            |
| Number of participating sites | 12 with 2 phases (intervention and control) each                                                                                                                                                                                                                                                                                                                                                                                                                                                |
| Planned sample size           | At least 18 patients per site and phase in 12 sites, thus n=432 in total; accounting for a patient drop-out of maximally 10%, 480 patients need to be included in total. Collecting data over 12 months per phase ensures inclusion of a sufficient number.                                                                                                                                                                                                                                     |
| Study intervention            | Hand disinfection alone (intervention, IV) versus hand disinfection plus gloves and gowns (control, CO)                                                                                                                                                                                                                                                                                                                                                                                         |
| Study population              | Participation criteria defined for sites and patients, see study protocol                                                                                                                                                                                                                                                                                                                                                                                                                       |
| Primary endpoints             | Gram-negative infection in newborn infants requiring intensive care and colonization screening                                                                                                                                                                                                                                                                                                                                                                                                  |
| Secondary endpoints           | 
Patient-level endpoints:
 
 
• any relevant transmission
 
• transmission with 2MRGN
 
• any bloodstream infection (BSI)
 
• 2MRGN BSI
 
• clinical infection
 
 
Month-level endpoints:
 
 
• at least one transmission
 
• at least one transmission with 2MRGN
 
• started antibiotics cycles
 
• percentage of days with antibiotics
 
 |

|                           |                                                                                                                                                                                                                                                |
|---------------------------|------------------------------------------------------------------------------------------------------------------------------------------------------------------------------------------------------------------------------------------------|
|                           | 
 
at least one started reserve antibiotic
 
                                                                                                                                                      |
| Statistical analyses      | Estimation of infection risk differences between IV and CO using generalized estimating equations (GEE) models for binary endpoints with identity link; test of non-inferiority with margin of 0.05 using one-sided significance level of 0.05 |
| Registration of the study | German Trial Register DRKS00019103                                                                                                                                                                                                             |

The study was approved by the institutional review board of the University of Lübeck (primary vote, 19-275) and by the review boards of all participating sites (secondary vote).

## 5 Database

The database is the data taken over from the clinical project management team according to Chapter 3. In this, data is documented entirely on an aggregated level, i.e., per month per site.

The data is structured as follows:

- Every of the 12 sites participates in the study in two phases, in one of which hand disinfection alone (IV), in the other hand disinfection plus gloves and gowns is applied (CO). The order of the two phases is randomized.
- Every phase has a duration of 12 months, so that for every site, data is collected for 24 months.
- Each of the two phases at one site is considered one cluster.
- Given the aggregation of the data in months, the observational unit is the month (month-level variables).
- Some variables give the count of patients with a specific event. From this and the number of admissions in that month, the number of patients without the specific events is constructed as well as data on patient-level is constructed for analyses (patient-level variables).

To obtain the count of patients without a specific event, the number of events is subtracted from the number of admissions [Aufnahmen\_Neo] rendering the following additional variables:

| Count of patients with the event
(original variable) | Count of patients without the event
(constructed variable) |
|---------------------------------------------------------|---------------------------------------------------------------|
| Anzahl_gramNeg_nurLOS                                   | Anzahl_gramNeg_nurLOS_negativ                                 |
| Transm_Patient                                          | Transm_Patient_negativ                                        |
| Transmission_2MRGN_Patient_SAE                          | Transmission_2MRGN_Patient_SAE_negativ                        |
| Anzahl_kl_Sepsis_allg                                   | Anzahl_kl_Sepsis_allg_negativ                                 |
| Anzahl_BKpos_Sepsis_allg                                | Anzahl_BKpos_Sepsis_allg_negativ                              |
| Anzahl_2MRGN_LOS                                        | Anzahl_2MRGN_LOS_negativ                                      |

To allow for patient-level description, the data set is re-structured to contain one line per patient based on the documented number of patients admitted to the site [Aufnahmen\_Neo]. In this, the following month-level variables are used to construct the following patient-level variables indicating presence or absence of the event:

| Variable                                     | Month-level
(original variable) | Patient-level
(constructed variable) |
|----------------------------------------------|------------------------------------|-----------------------------------------|
| Gram negative infection                      | Anzahl_gramNeg_nurLOS              | gramNeg_nurLOS                          |
| At least one suspected transmission          | Transm_Patient                     | Transm                                  |
| At least one suspected transmission of 2MRGN | Transmission_2MRGN_Patient_SAE     | Transm2m                                |
| Clinical infection                           | Anzahl_kl_Sepsis_allg              | Sepsis                                  |
| Any BSI                                      | Anzahl_BKpos_Sepsis_allg           | Sepsis_pos                              |
| 2MRGN BSI                                    | Anzahl_2MRGN_LOS                   | LOS                                     |

For the estimation of the GEE models, a cluster variable [Cluster] is created that combines the information from the site identifier [Klinik\_ID] with the variable indicating the phase [Randomisierung], so that every site corresponds to two clusters, one for every phase.

The variable counting the number started reserve antibiotics in a month [Anzahl\_beg\_Reserve\_ATB] is dichotomized to indicate whether at least one treatment with a reserve antibiotic was started or not [Beg\_Reserve\_ATB].

In addition, the clinical project management team surveys the participating sites about consumption of disinfectant and estimated costs. This data will separately be transferred to the IMBS for analysis.

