Out of 319 infants, 47 (14.7%) were colonized with an MRGN pathogen, of which 30 infants (9.3%) tested positive for a 2MRGN pathogen. One infant was colonized with 2MRGN *E. coli* at birth, 15 infants were colonized within the first 5 weeks of life (figure 1). The 2MRGN pathogens were isolated from pharyngeal swabs (n=12), rectal swabs or fecal samples (n=19) or conjunctiva (n=1). Four infants were colonized with > 1 MDRO including two infants with MRSA and 3MRGN *E.coli* and two infants with 2MRGN *Enterobacter cloacae* and either 2MRGN *E.coli* or 2MRGN *Klebsiella pneumoniae*. Colonization with 2MRGN occurred at a median of 33 days. Figure 1 describes the timepoint of first colonization with MDRO in vulnerable infants. Seven infants were initially colonized with antibiotic susceptible bacteria and acquired 2MRGN features during hospital stay.

Out of 319 of infants, 296 received antibiotic therapy for a median duration of 7 days, 252 infants were already started on antibiotics on day 1 of life. MDRO colonized infants were treated for a median of 7 days. Among 2MRGN colonized infants, one infant developed a 2MRGN *E.coli* sepsis on day 6 of life, two infants were diagnosed with 2MRGN sepsis (*Enterobacter* spp.) between day 7 and 28 of life and five infants were treated for culture-negative sepsis. Our data are in line with previous single center studies in Germany with evidence of MDRO colonizing infants in 4.9% of 635 neonates, 12.7% of 584 screened neonates and 15.3% of 1407 preterm infants, respectively (20-22). In a recent multicenter RCT on the effect of probiotics to prevent MDRO colonization in preterm infants 28-32 weeks of gestation, we confirmed center-specific MDRO colonizing rates between 5-20% (23). In the BALTIC trial, we therefore estimated the number of 2MRGN colonized infants to be 10% during the hospital stay.

[figure not shown]

**Figure 1:** First detection of MRGN, MRSA, MRSA or Vancomycin resistant enterococci (VRE)

MRDO = Multi-drug resistant organisms; KRINKO = German Commission on Hospital Hygiene and Infection Prevention, MRGN = Multidrug-resistant Gram negative bacteria, 2MRGN (resistant to Piperacillin and Cefotaxim or Ceftazidim), 3MRGN (resistant to Piperacillin and Cefotaxim or Ceftazidim and fluorquinolones), MRSA = methicillin-resistant *Staphylococcus aureus*, VRE = Vancomycin resistant *Enterococci*

Additional first detections after the 15th week of life: n = 4 2MRGN pathogens

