### *Outcomes*

The primary endpoint is the rate of HA bloodstream infections with Gram-negative pathogens in all preterm and newborn infants who received colonization screening. This outcome is defined clinically according to NEO-KISS criteria (at least two clinical signs of sepsis + one laboratory sign, e.g. increase in C-reactive protein > 10mg/l) after 72 hours of life and requires the detection of a Gram-negative pathogen in the blood culture. Blood-culture isolates will be sent from the study centers to the study management.

Key secondary endpoint is the 2MRGN transmission rate which is assumed if another infant is colonized with the same 2MRGN pathogen after 2MRGN colonization or infection of an infant

requiring intensive care in a temporal (maximum 90 days) and spatial context (potential contact in the intensive care unit) (26). This assumption is made if, in addition to pathogen identification, the antimicrobial susceptibility testing patterns are identical. Suspected transmission of or bloodstream infection with an 2MRGN pathogen will be reported to the study management as severe adverse event within 24 hours.

Transmission/outbreak management remains the responsibility of the local interdisciplinary infection control team and is carried out according to local standards, including the decision whether to initiate genetic identity testing in the acute situation. 2MRGN isolates will be shipped from local sites and molecular typing will be performed at the Department of Infectious Diseases and Medical Microbiology at the University of Lübeck. Other secondary outcomes at the level of study sites per period ("study phase") are:

- Rate of clinical and culture proven infections
- Rate of infection outbreaks
- Number of initiated antibiotic cycles
- Duration of antibiotic treatment (days)
- Exposure to reserve antibiotics, including Carbapenems per study site in % infants.

To assure documentation of relevant outcomes, intensive interdisciplinary collaboration (neonatology/infectiology/hygiene/pharmacy/management) is required. Data are collected by monthly cluster report forms on infection and transmission rates and yearly surveillance of antibiotic use, disinfectant consumption, and cost estimations.

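### The SAP analyses 2MRGN transmission only as suspected and gives no role to the central typing that the protocol plans for detecting it

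*Combined protocol and SAP*

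**What the plan says.** The protocol (Outcomes) makes the 2MRGN transmission rate the key secondary endpoint. Transmission is one "which is assumed if another infant is colonized with the same 2MRGN pathogen after 2MRGN colonization or infection of an infant", within at most 90 days and with potential contact in the unit. The laboratory criterion is phenotypic: "This assumption is made if, in addition to pathogen identification, the antimicrobial susceptibility testing patterns are identical". Sites are the source of the events: "Suspected transmission of or bloodstream infection with an 2MRGN pathogen will be reported to the study management as severe adverse event within 24 hours".

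The same section adds that "2MRGN isolates will be shipped from local sites and molecular typing will be performed" centrally. The Data management section says why isolates are kept with their collection date: to allow a temporal and "cluster-related assignment (retrospective detection of transmission by central biobanking and pathogen genotyping").

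SAP Section 5 builds the patient-level variable Transm2m from the monthly count Transmission_2MRGN_Patient_SAE, and Section 9.4.1 uses the monthly yes/no variable Transm_2MRGN_j_n. Both carry the label "At least one suspected transmission of 2MRGN". The effect measure is a risk difference with identity link, and Sections 9.4.1 and 9.4.2 class these analyses as descriptive. The SAP names no typing-confirmed variable, no reclassification step and no sensitivity analysis that uses typing.

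**The concern.** Gloves and gowns can only act on spread from one infant to another. The phenotypic rule also admits pairs that share species and antibiogram by coincidence. The protocol's benchmarking cohort shows that infants do not all become carriers in the same way: one carried 2MRGN *E. coli* at birth, and "Seven infants were initially colonized with antibiotic susceptible bacteria and acquired 2MRGN features during hospital stay". Whether any given acquisition was spread within the unit is what typing could settle.

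At stake is how the key secondary endpoint can be read. False events add noise and, on some scales, make the two regimens look more alike. The regimen is open (SAP 4.1), so the readiness to suspect transmission may also differ between phases. If the role of typing is settled only after the suspected-transmission results are known, the choice becomes post hoc.

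**Working it through.** **The plan's own figures.** The documents give no transmission rate, no share of suspected events that typing would refute, and no power for this endpoint. The stated sample size belongs to the primary endpoint. It reproduces (Farrington-Manning: 182.6 per arm × design effect 1.17 / 12 sites = 17.8, so 18 per site and phase, 432 in total, 480 with 10% drop-out) but does not bear on this point.

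**Inputs.** From the protocol's sample size section: 150 admissions per centre and year, so 150/12 = 12.5 per site-month and 12 × 150 = 1,800 per regimen. Assumed: true transmission risk per infant of 1% vs 2%, 2% vs 3% and 2% vs 4% (control vs intervention), and 20%, 40% or 60% of suspected control events false.

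**Step 1: equal false-event risk q in both phases, independent of true transmission.**

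- q ≈ p_control × share / (1 − share). For 2% and 60%: 0.02 × 0.6/0.4 = 0.03.
- Patient level: observed risk = p + (1 − p)q, so observed RD = (1 − q) × true RD.
- Month level: P(at least one) = 1 − (1 − p)^12.5, so observed RD = (1 − q)^12.5 × true RD.

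| True risks | False share | q | Patient RD, true → observed | SE ratio | Month RD, true → observed | Month factor |
|---|---|---|---|---|---|---|
| 1% vs 2% | 20% | 0.0025 | 0.0100 → 0.00998 | 1.08 | 0.1051 → 0.1019 | 0.969 |
| 1% vs 2% | 60% | 0.0150 | 0.0100 → 0.00985 | 1.40 | 0.1051 → 0.0870 | 0.828 |
| 2% vs 3% | 60% | 0.0300 | 0.0100 → 0.0097 | 1.45 | 0.0935 → 0.0639 | 0.683 |
| 2% vs 4% | 20% | 0.0050 | 0.0200 → 0.0199 | 1.08 | 0.1765 → 0.1658 | 0.939 |
| 2% vs 4% | 40% | 0.0133 | 0.0200 → 0.01973 | 1.19 | 0.1765 → 0.1492 | 0.846 |
| 2% vs 4% | 60% | 0.0300 | 0.0200 → 0.0194 | 1.38 | 0.1765 → 0.1206 | 0.683 |

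The two scales behave differently because one infant is rarely both a true and a false event, whereas a month with 12.5 admissions often contains both. With q = 0.03 the patient-level factor is 0.97 and the month-level factor is 0.97^12.5 = 0.683.

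**Step 2: false-event risk differs by phase.** Take true risks of 2% vs 3% and a control q of 0.01.

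- Intervention q = 0.005: patient RD = (0.03 + 0.97 × 0.005) − (0.02 + 0.98 × 0.01) = 0.03485 − 0.0298 = 0.005, against a true 0.010. Month RD = (0.98 × 0.99)^12.5 − (0.97 × 0.995)^12.5 = 0.685 − 0.642 = 0.043, against a true 0.0935.
- Intervention q = 0.02: patient RD = 0.0494 − 0.0298 = 0.020. Month RD = 0.685 − 0.531 = 0.154.

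Both measures can move either way.

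**Step 3: missed transmissions.** The phenotypic rule can also miss spread, for example when the antibiogram changes. With sensitivity Se equal in both phases and q = 0.01, observed patient RD = (Se − q) × true RD: a true 0.010 becomes 0.0089 at Se = 0.9 and 0.0049 at Se = 0.5. The documents give no sensitivity either.

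**The case against.** **The SAP analyses what the protocol defines.** This stands. The definition has explicit criteria (pathogen, antibiogram, time, contact), so a reader who infers that the SAP departs from the protocol's endpoint, or that sites apply an unguided judgement, goes too far. The gap is an unused result, not a deviation.

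**A reader might infer that a real difference is certain to be pulled toward none, in favour of the intervention.** The documents do not support this. Step 1 needs equal error in both phases, which an open trial does not guarantee. Even with equal error, the patient-level risk difference hardly moves. Set the suspected control events to 1, let a share f be false, and let true transmission double. The suspected events are then 1 and 2 − f, and their difference is 1 − f. The true difference is 2(1 − f) − (1 − f) = 1 − f, the same. Only the ratio falls, and the SAP estimates no ratio.

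**A reader might also take the cohort's seven converters and one infant positive at birth, 8 of 30 carriers, as the false share.** The denominator is all carriers, not suspected transmissions. A converter may have acquired the strain from another infant, and no typing is reported for that cohort.

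**The analysis is descriptive, and the SAP covers only the biometry institute's work (SAP 2).** Both are true. No formal non-inferiority conclusion rests on this endpoint, and a typing analysis may be planned elsewhere. The documents describe none; if one exists, a cross-reference would close much of the gap.

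**Aggregated data limit what can be done.** The database holds site-month totals, and isolates carry no identifying data. This rules out demanding that admission-positive infants be excluded, unless sites can supply that count. A positive infant on arrival also does not readily fit a rule that requires potential contact in the unit. It does not rule out a count per site-month, since date and cluster are kept.

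**Conclusion.** The point holds in this form: the key secondary endpoint is analysed only as suspected transmission, while a better measurement that the protocol already plans has no stated role.

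If false events are equally frequent in both phases, the patient-level risk difference keeps 97.0 to 99.75% of its value with a standard error 8 to 45% larger, and the month-level risk difference loses about 3 to 32%. This rests on assumed risks of 1 to 4%, an assumed 20 to 60% false share, 12.5 admissions per site-month and independent events. If error differs by phase, the direction is open on both scales. Because the analysis is descriptive, this is a worthwhile improvement and not a threat to the primary conclusion.

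**What to change.** In SAP 9.4.1, and in 9.4.2 where counts can be formed, pre-specify before database closure an analysis of typing-confirmed 2MRGN transmission per site-month: an isolate indistinguishable on central typing from that of an earlier carrier in the same unit within 90 days. Report it beside the protocol-defined suspected transmission, which stays as the endpoint. State that:

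- the laboratory decides relatedness without knowledge of phase; since date and cluster could reveal phase, use coded isolates and apply the date and unit rule afterwards;
- suspected cases without a typed isolate are shown separately, by phase;
- repeat isolates from one infant are not counted as a second carrier, which needs a pseudonymous infant code or one isolate per infant;
- infants positive at the admission screen are shown separately only if sites can supply that count.

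While 9.4.2 is open, correct its variable pairing. The entry for 2MRGN transmission names the Gram-negative infection variable, the entry for 2MRGN BSI names the 2MRGN transmission variable, and Anzahl_2MRGN_LOS is missing from the analysed pairs.

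The cost is SAP wording and a merge of typing results into the site-month data. The downside is fewer counted events and some missing isolates.
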